## Abstract

**Background:**

Chronic nonspecific low back pain (CNSLBP) is the most common chronic condition worldwide. Although recommended in several clinical guidelines, high-quality double-blind studies supporting the evidence for acupuncture remain limited.

**Objective:**

This study aims to test the efficacy of penetrating acupuncture for CNSLBP using double-blind needles that blind both the acupuncturist and the participant, which provides the most rigorous methodology for acupuncture trials to date.

**Methods:**

This study was a randomized double-blind (acupuncturist-patient) placebo-controlled trial conducted at the Tokyo Ariake University of Medical and Health Sciences Acupuncture Clinic. Seventy-five adult participants with CNSLBP were randomized to genuine penetrating, skin-touch placebo, and no-touch placebo needles that do not touch the skin. Consistent with prior studies and clinical practice, acupoints on the bladder meridian were mainly used. The study has 2 primary outcomes: an objective outcome and a subjective outcome. The primary objective outcome is the flexion-relaxation phenomenon, an index associated with low back pain, assessed using surface electromyography (sEMG) recordings of the bilateral lumbar erector spinae muscles and hamstrings. The primary subjective outcome is pain intensity measured using a visual analog scale (VAS) before and after the intervention.

**Results:**

The Ethics Committee approved the study protocol of Tokyo Ariake University of Medical and Health Sciences in April 2018 (approval number: 0246). This study started in July 2018 and was completed in March 2025.

**Conclusions:**

This trial used a double-blind design and objective outcome measures to rigorously evaluate the efficacy of acupuncture for CNSLBP.

## Introduction

Low back pain (LBP) is one of the most common chronic conditions and has a lifetime prevalence of approximately 50%‐84% worldwide [1-3]. The Japanese Ministry of Health reported that the rate of subjective symptoms (91.2 men and 113.3 women per 1000 population) makes LBP the most common chronic complaint in Japan [4]. The medical costs of work-related LBP in Japan were estimated to be 82.14 billion yen (746.72 million euro or US $1.027 billion) in 2011 [5].

LBP can be divided into 2 types: specific LBP caused by structural disorders of the spine, such as spinal stenosis and radiculopathy, or another internal organ causing referred pain; and nonspecific LBP with no apparent cause, which accounts for the majority (85%) of LBP cases [6]. Over 50% of patients with acute nonspecific LBP do not consult a health care provider. Most patients who consulted a health care provider still had pain after 3 months that developed into chronic nonspecific LBP (CNSLBP) [7]. Pathoanatomical, physical, neurophysiological, psychological, and social factors are associated with inducing and aggravating CNSLBP [8]. Patients with CNSLBP do not improve if these associated factors are not considered by their health care provider, which then results in patients receiving standardized, monotonic treatments [7].

Physiological studies using surface electromyography (sEMG) reported the absence of the flexion-relaxation phenomenon (FRP) [9-11] in patients with CNSLBP. FRP is an electrical silencing of the erector spinae muscles with full trunk flexion. The absence of FRP is attributed to abnormal tissue loading and pain that is mechanically provoked due to maladaptive movements as compensation for injury and impaired motor control [9,11,12]. The FRP is typically absent in patients with LBP, making it a clinically relevant physiological marker. As an objective neuromuscular indicator, FRP may be particularly valuable in placebo-controlled trials for detecting genuine treatment effects [12,13]. Therefore, evaluation of FRP is especially useful in placebo-controlled clinical trials of acupuncture, where sham acupuncture might have a greater effect on self-reported pain than a placebo pill [14,15].

The main treatment for CNSLBP is nonsteroidal anti-inflammatory drugs (NSAIDs). NSAIDs have shown small to moderate pain improvement as compared with a placebo pill in most systematic reviews [16]. However, the Agency for Healthcare Research and Quality indicated that NSAIDs administered for LBP are associated with gastrointestinal and cardiovascular adverse events [17] and adverse drug reactions such as gastric ulcer with bleeding and anemia, myocardial infarction, stroke, and acute kidney trauma [18]. If there is no improvement with NSAIDs, opioids are often prescribed [19], despite a lack of evidence that supports the efficacy of opioids for CNSLBP [20,21] as well as the risk of habituation [19].

Many clinical guidelines recommend acupuncture for CNSLBP [22,23]. Meanwhile, the use of acupuncture is controversial for the treatment of CNSLBP due to the lack of high-quality evidence to support its efficacy [23]. A 2005 Cochrane review reported that acupuncture is more effective than sham interventions as a short-term measure for treating CNSLBP [24]. In contrast, the National Institute for Health and Care Excellence in the United Kingdom does not recommend acupuncture for LBP with or without sciatica [25]. Recent systematic reviews have continued to report modest short-term benefits of acupuncture for chronic nonspecific low back pain; however, the overall certainty of evidence remains low to moderate due to methodological limitations, including inadequate blinding, physiologically active sham controls, and reliance on subjective outcomes [26].

Behind these inconsistent conclusions, there is a fundamental issue of acupuncture research, that is a suitable placebo control for acupuncture needling. Some studies used shallow needling or needling in the wrong points as a placebo control. However, these placebo controls are inappropriate because needles are inserted into the body, whether shallow, at the wrong points, or not [27,28]. To solve this issue, Streitberger et al [29], in 1998, developed a single-blind (patient masking) placebo needle that does not penetrate the skin. Many clinical studies have used the Streitberger needle to demonstrate the effectiveness of acupuncture. This placebo needle that presses the skin has been used in acupuncture studies as the best device to minimize patient bias because it has been considered almost impossible to double-blind both patients and acupuncturists [30-32]. In clinical trials that used these single-blind placebo needles [29,33], the efficacy of the genuine acupuncture group was not revealed compared to that of the placebo group [26,34]. Therefore, researchers have argued that results can be distorted using sham acupuncture, including the Streitberger needle, which is not physiologically inert [35]. In addition to the placebo not being physiologically inert, unblinded practitioners could have influenced how the patients responded [36], which introduces bias, strongly indicating the need for double-blinding in acupuncture research [34,37]. To solve these problems, our team developed a double-blind needle that could blind both patients and acupuncturists, which consists of 3 needle types, including a genuine needle and 2 types of placebo needles. The placebo needles include a skin-touch needle similar in structure to the conventional, physiologically active needle and a no-touch, physiologically inert needle [38-43]. Thus, it is imperative to conduct randomized placebo-controlled trials of acupuncture under double-blind conditions since these studies have not been conducted [30-32].

The primary aim of this study was to determine whether penetrating acupuncture produces greater improvements in FRP and pain intensity compared with both skin-touch placebo and no-touch inert placebo needles.

In summary, our double-blind acupuncture clinical trial for CNSLBP offers rigorous testing of a critical treatment for LBP that will advance acupuncture and placebo science. Our trial methodology addresses the following: (1) lack of practitioner blinding, (2) use of noninert placebo needles, and (3) lack of objective measures for the evaluation of LBP. The aims of our study are to (1) determine the efficacy of genuine penetrating acupuncture versus skin-touch placebo needles versus no-touch placebo needles and (2) assess the intervention effect using sEMG to record FRP, an objective measure of CNSLBP.

## Methods

### Study Design and Setting

This study is a single-center, randomized double-blind (acupuncturists and participants), placebo-controlled trial consisting of 3 treatment arms, including genuine penetrating needles (penetrating group), skin-touch needles (skin-touch group), and no-touch needles that do not touch the skin (no-touch group) [38-45]. This study was being conducted at Tokyo Ariake University of Medical and Health Sciences (TAU) Acupuncture Clinic and Medical Clinic, Japan. The study flow chart is shown in Figure 1.

**Figure 1. F1:**
[figure not shown]
Study flow diagram. JOABPEQ: Japanese Orthopaedic Association Back Pain Evaluation Questionnaire; MASS: Massachusetts General Hospital Acupuncture Sensation Scale; RMDQ: Roland-Morris Disability Questionnaire; sEMG: surface electromyography; VAS: visual analogue scale.

### Sample Size

We calculated effect sizes and sample sizes using G*Power 3.1.9.6 (Heinrich-Heine-Universität, Düsseldorf). Results from a previous study of CNSLBP that determined the effects of high-velocity spinal manipulation on paraspinal muscle activity with sEMG found an effect size of 0.51 [46]. Based on this effect size, with a statistical power of 95% and an alpha of 5%, the sample size was calculated to be 63 participants (21 participants in each group). However, in our study, we conduct X-ray examinations at TAU Medical Clinic as a screening test for CNSLBP. Therefore, with a potential dropout rate of 20%, we recruited a total of 75 participants (25 participants in each group).

Because prior randomized trials evaluating acupuncture effects on FRP are lacking, the effect size was derived from the most physiologically comparable intervention study examining paraspinal muscle activity. The target power was set at 95% to reduce the probability of Type II error and to enhance the stability of the estimate in this mechanistic trial.

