### Randomization

In total, 75 sets of double-blind needles were prepared and placed in separate bags numbered 1-75 (25 sets of 40 penetrating acupuncture needles, 25 sets of 40 skin-touch acupuncture needles, and 25 sets of 40 no-touch acupuncture needles). Seventy-five participants were randomly assigned 1:1:1 to the penetrating needle group, the skin-touch needle group, or the no-touch needle group by an independent investigator using a random numbers table that was generated by the RAND function (Microsoft Office Excel 2007).

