### Statistical Analysis

Baseline characteristics will be assessed using Fisher exact test, ANOVA, and the Levene test. To evaluate the primary and secondary outcomes, we will use a linear mixed-effects model to account for the variability between groups and over time. This model will include “treatment group,” “time,” and their interaction as fixed effects. To address the potential influence of practitioner-related differences, “practitioner ID” will be included as a random effect. For post-hoc analyses, the Bonferroni correction will be applied to adjust for multiple comparisons. For nonnormally distributed data, the Mann-Whitney *U* test, Friedman test, or Kruskal-Wallis test will be used as appropriate. Blinding success will be evaluated by comparing the proportion of correct guesses in each group against chance level (33.3%) using a chi-square goodness-of-fit test. In addition, Bang Blinding Index will be calculated for both participants and acupuncturists to quantify the degree of blinding [55,57]. A Blinding Index close to 0 indicates successful blinding, whereas values approaching ±1 indicate unblinding. To account for variability among acupuncturists, analyses will be conducted under an intention-to-treat framework. Missing outcome data will be handled using multiple imputation under the assumption of missing at random. All statistical analyses will be conducted using SPSS Statistics version 31 (IBM SPSS Statistics) and R (R Foundation for Statistical Computing). Statistical significance will be set at a 2-sided *P* value of <.05.

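### The stated 95% power fits a three-group omnibus test on the sEMG outcome, not the primary aim of beating both placebos, and the VAS co-primary has no power figure

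*Protocol article*

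**What the plan says.** The protocol article contains one power calculation, under Methods, Sample Size. It cites a previous spinal-manipulation study that, for "paraspinal muscle activity with sEMG found an effect size of 0.51". It then reports that "with a statistical power of 95% and an alpha of 5%, the sample size was calculated to be 63 participants", 21 per group. The software is named ("We calculated effect sizes and sample sizes using G*Power 3.1.9.6"), but the test and the effect-size metric are not. After an allowance for dropout the target became 75: "with a potential dropout rate of 20%, we recruited a total of 75 participants (25 participants in each group". The section justifies the 95% target partly as a way to make a Type II error less likely.

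The Introduction gives the primary aim as whether "penetrating acupuncture produces greater improvements in FRP and pain intensity compared with both skin-touch placebo and no-touch inert placebo needles". The Discussion (Principal Findings) repeats this as the hypothesis. Primary Outcomes lists two co-primary outcomes: the immediate change in FRP and the immediate change in VAS pain. Statistical Analysis plans a mixed model with group, time and their interaction, and adds: "For post-hoc analyses, the Bonferroni correction will be applied to adjust for multiple comparisons". The number of comparisons is not given. The general level is stated as "Statistical significance will be set at a 2-sided *P* value of <.05".

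**The concern.** With three arms, a calculation that uses one effect size and one alpha, with no adjustment for pairwise testing, is usually an omnibus test. An omnibus test can reject because the two placebos differ from each other, or because penetrating beats only one of them. Neither result answers the stated aim, which needs penetrating to be better than skin-touch and also better than no-touch. Power for that is lower than power for the omnibus test.

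The consequence is for interpretation. A reader who takes 95% as the trial's power may treat a non-significant penetrating-versus-skin-touch comparison as good evidence that penetration adds nothing, although the trial may have had a much smaller chance of detecting that difference. For VAS there is no power figure at all.

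**Working it through.** **Inputs from the protocol article.** Effect size 0.51, power 95%, alpha 5%, N = 63 (Sample Size); three arms, 1:1:1 (Randomization); two-sided testing and Bonferroni without a count (Statistical Analysis); 25 per group recruited (Sample Size).

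**Assumptions.** 0.51 is Cohen's f; Bonferroni covers three comparisons, two, or none; the pattern of means is one of the two below; no precision is gained from baseline, because no pre-post correlation is given.

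**Step 1: reproduce 63.** For a one-way omnibus F test the noncentrality is λ = N·f², with 2 and N − 3 degrees of freedom.
- N = 60: λ = 60 × 0.2601 = 15.61, power 0.941.
- N = 63: λ = 63 × 0.2601 = 16.39, power 0.952.

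So 63 is the smallest equal-group total that reaches 95%. A group-by-time interaction with f = 0.255, two times and correlation 0.5 has λ = 63 × 0.255² × 2/0.5 = 16.39 with the same degrees of freedom. It is the same 2-df test in another form. A two-arm t test at d = 0.51 would need about 100 per arm, so 63 does not come from a pairwise comparison at that effect size.

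**Step 2: turn f into pairwise differences (SD units).**
- Placebos equal, means (d, 0, 0): f = d√2/3, so d = 0.51 × 3/√2 = 1.08 against each placebo. For a fixed f this is the most favourable pattern for beating both.
- Skin-touch midway, means (d, d/2, 0): f = d/√6, so d = 0.51 × √6 = 1.25 against no-touch and 0.62 against skin-touch. This pattern is illustrative.

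**Step 3: power of one comparison.** Noncentral t with noncentrality d√(n/2) and pooled df 3n − 3. For n = 21 and d = 1.08 the noncentrality is 1.082 × √10.5 = 3.51. At alpha 0.05/3 this gives 0.848. At n = 25 it is 0.912. Against a midway skin-touch arm the figures are 0.338 and 0.409.

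**Step 4: power to beat both placebos, FRP only.** Simulation of the two t tests with the shared penetrating arm and pooled variance, 200,000 runs:

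| Pattern | n per group | Bonferroni for 3 | Bonferroni for 2 | Uncorrected |
|---|---|---|---|---|
| Placebos equal | 21 | 0.757 | 0.808 | 0.882 |
| Placebos equal | 25 | 0.853 | 0.889 | 0.938 |
| Skin-touch midway | 21 | 0.335 | 0.394 | 0.512 |
| Skin-touch midway | 25 | 0.410 | 0.471 | 0.586 |

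For comparison, the omnibus test has power 0.952 at 21 per group and 0.979 at 25. Every entry in the table lies below 0.95.

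**The case against.** **The test is inferred.** The article names neither the test nor the metric, and the source study is not at hand. This stands as a limit. The match at 63 is exact and the other standard variants tried do not give it, apart from the equivalent interaction form. Even so, the authors should confirm the test.

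**The size of the gap rests on assumptions.** This also stands. The Bonferroni count is not stated, the aim itself involves only two comparisons, and if both must succeed one can argue that no correction is needed. The table therefore shows all three cases. The midway pattern is not in the article either. The Introduction likens the skin-touch needle in structure to a physiologically active one, and the Discussion says active shams mask acupuncture's effect, but neither gives a magnitude for FRP. The 34% to 59% figures are illustrations.

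**Stronger readings the article does not support.**
- That 63 is a miscalculation: it is correct for the inputs as read here.
- That the authors claim 95% power for the pairwise comparisons or for VAS: the Type II error remark is general and is tied to neither.
- That the chance of missing the effect is always several times 5%: at 25 per group with equal placebos, a single comparison under three-way Bonferroni misses 9% of the time.
- That the trial must succeed on both outcomes, so power is lower still: the aim joins FRP and pain with "and", but no decision rule says that both must be significant, and no VAS effect size is given from which to compute the loss.

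**Sizing on one primary outcome is common, and data collection is finished.** Both are true. They limit the remedy to the text but do not make the 95% describe the primary aim.

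**Conclusion.** The point holds as a mismatch between the calculation and the aim. The only stated power fits a 2-df omnibus test on the sEMG outcome, while the primary question is whether penetrating beats both placebos on FRP and pain. With f = 0.51 and the most favourable pattern of means, the chance of missing at least one of the two FRP comparisons is 12% to 24% at 21 per group (100% minus 88%, 81% or 76%) and 6% to 15% at 25 per group, against the 5% that a 95% figure implies. With skin-touch midway, power falls to 34% to 51% and 41% to 59% respectively. That the figure lies below 95% does not depend on the Bonferroni count; how far below depends on the count and on the pattern of means. For VAS the article supports no figure.

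**What to change.** In the Sample Size section:
1. Name the test and the effect-size metric to which the 95% applies.
2. Give the power for penetrating versus each placebo, and for beating both, at 21 and 25 per group. Present it as a range, with the Bonferroni count and the pattern of means labelled as assumptions.
3. State that VAS was not separately powered.
4. Limit the Type II error statement to the test that the 95% covers.

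The cost is wording only. Data collection ended in March 2025, so no participants are added and no analysis changes. The stated power becomes less favourable.

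### The 20% dropout allowance is miscalculated: 75 participants leave 63 evaluable only up to 16% loss, though the effect on power is small

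*Protocol article*

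**What the plan says.** The protocol article's Sample Size section takes an effect size of 0.51 from an earlier spinal manipulation study, sets power at 95% and alpha at 5%, and reports that "the sample size was calculated to be 63 participants (21 participants in each group". It then remarks that "we conduct X-ray examinations at TAU Medical Clinic as a screening test for CNSLBP" and continues directly: "Therefore, with a potential dropout rate of 20%, we recruited a total of 75 participants (25 participants in each group". It names G*Power as the software, but neither the effect-size metric nor the test.

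The Randomization section says "Seventy-five participants were randomly assigned 1:1:1" and describes 75 prepared needle sets, 25 of each type. The Recruitment section also gives 75 enrolled. So 75 is the number randomised, not the number screened.

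**The concern.** Two things look wrong in the same paragraph.

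- **The arithmetic.** An allowance for dropout should leave the required number once the assumed loss has occurred. Here it does not: the section's own loss rate, applied to its own recruited number, gives fewer than its own required number.
- **The rationale.** An X-ray screen removes people before they enter the trial. Dropout removes people after they enter. The paragraph uses the first to justify an allowance for the second, so a reader cannot tell which loss the 20% describes.

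At stake is the accuracy of the sample-size statement. The section presents 95% power as a deliberate choice, so the numbers behind it should agree before results are reported against them.

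**Working it through.** **Inputs.** From Sample Size: effect size 0.51, power 0.95, alpha 0.05, required N = 63 (21 per group), dropout 20%, recruited N = 75 (25 per group). From Randomization: three equal arms, 75 randomised.

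**Step 1: reproduce the 63.** Assume 0.51 is Cohen's f and the test is a one-way omnibus ANOVA with k = 3 groups. Power is the probability that a noncentral F variable with 2 and N − 3 degrees of freedom and noncentrality λ = N × f² exceeds the 5% critical value. Here f² = 0.51² = 0.2601. The smallest balanced N with power of at least 0.95 is 63, an exact match with the plan.

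Other readings were tried:

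- A group-by-time interaction with f = 0.255, two time points and correlation 0.5 has λ = N × 0.255² × 2/(1 − 0.5) = N × 0.2601, with the same degrees of freedom, so it also gives 63.
- A one-way ANOVA with f = 0.255 gives 243 in total.
- A pairwise comparison with d = 0.51 gives 100 per group.

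The last two do not reproduce the plan.

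**Step 2: check the allowance.** This step needs no assumption about the test.

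- Required with 20% loss: N/(1 − d) = 63/0.8 = 78.75, so 79. With equal arms, 21/0.8 = 26.25, so 27 per arm and 81 in total.
- Left from 75 after 20% loss: 75 × 0.8 = 60, or 20 per arm. This is 3 below 63.
- Largest loss that keeps 63: 1 − 63/75 = 0.16, or 12 of 75.
- Likely origin of 75: N × (1 + d) = 63 × 1.2 = 75.6 (25.2 per arm), rounded down.

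The recruited number is therefore 4 short of 79, or 6 short of 81.

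**Step 3: effect on power**, under the assumption in Step 1.

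| Analysed N | λ = N × 0.2601 | Omnibus power |
|---|---|---|
| 60 (20% loss) | 15.61 | 94.1% |
| 63 (16% loss) | 16.39 | 95.2% |
| 75 (no loss) | 19.51 | 97.9% |

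At 20% loss the shortfall against the target is 95.0 − 94.1 = 0.9 percentage points.

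**Step 4: where the X-ray falls.** Telephone Screening sends callers who meet the criteria to the clinic for an examination and X-rays to establish the diagnosis. Baseline Assessment places the X-ray before the baseline questionnaires. Treatment Procedure has the acupuncturist tell participants, immediately before treatment, that they are about to be allocated. On this sequence a person excluded by X-ray is a screen failure and is not among the 75 randomised.

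**The case against.** The strongest reply is that nothing of substance follows, and most of it stands.

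- **Power.** A reader might infer that the trial misses its power target. That is true only to the decimal, at 20% loss: 94.1% against 95%. If all 75 are analysed, power is 97.9%, above target.
- **Likelihood of 20% loss.** Both co-primary outcomes are changes measured immediately after a single session, so losing a fifth of them is pessimistic. Attrition up to one week affects secondary outcomes only. The Statistical Analysis section also plans multiple imputation, which keeps participants with missing outcomes in the analysis, although it does not fully restore the lost information.
- **Meaning of the 20%.** If it stood for X-ray exclusions, the 75 randomised already exceed 63 and there is no shortfall. The arithmetic error and this reading of the rationale are alternatives and should not be added together. This reading does not rescue the paragraph, however: dropout would then be the wrong word, 75 should not be the number randomised, and no separate allowance for later loss would be stated.
- **Intention to treat.** A reader might infer that X-ray exclusions were removed after randomisation, against the intention-to-treat framework in Statistical Analysis. No section says so, and the described sequence points the other way.
- **The test.** The power figures are for an omnibus ANOVA whose metric is inferred, whereas the planned analysis is a linear mixed-effects model with Bonferroni-adjusted comparisons. They check the sample-size calculation; they do not give the power of the final analysis.

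What remains is that 63, 20% and 75 are all stated in one paragraph and are mutually inconsistent as a dropout allowance.

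**Conclusion.** The point holds as a minor error of arithmetic and wording. Seventy-five randomised participants cover 16% loss, not 20%; a 20% allowance on 63 needs 79, or 81 with equal arms. This follows from the stated figures alone.

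The consequence is small: about 0.9 percentage points of omnibus power at 20% loss, and none if loss stays at or below 16%. These power figures assume that 0.51 is Cohen's f in a three-group omnibus ANOVA or an equivalent parameterisation. The document does not name the metric, but this reading reproduces 63 exactly.

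The X-ray sentence is at fault only as an unclear rationale. The document does not show a materially underpowered trial, a breach of intention to treat, or a need for more participants.

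**What to change.** Reword the Sample Size paragraph as follows.

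1. State that 75 randomised participants allow for up to 16% loss with 63 evaluable (21 per group), and that at 20% loss 60 remain (20 per group), with omnibus power of about 94%.
2. Name the effect-size metric and the test used in G*Power, so that the 63 and the 94% can be checked. If the sponsor's record shows something other than Cohen's f in a three-group omnibus ANOVA or an equivalent parameterisation, recompute the power figure on that basis.
3. Say whether the 20% refers to loss after randomisation or to X-ray screening exclusions. The X-ray sentence may stay if it explains why more people were screened, but it should not stand as the reason for a dropout allowance.
4. Report X-ray exclusions as screen failures, outside the 75 randomised.

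The cost is one paragraph and a slightly less favourable stated allowance. The Results section says that data collection finished in March 2025; no participants, procedures or analyses change.
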